# 5 STUDY SETTING

This is a single-centre study. Recruitment, intervention and data collection will take place on the Neonatal Intensive Care Unit at King’s College Hospital, [name]. The unit routinely cares from preterm ventilated infants and has previous experience on the use of OxyGenie in the context of trials. Participants will be identified by clinical staff and their parents will be approached and consented by the investigators.

**6 SAMPLE AND RECRUITMENT**

- 1. **Eligibility Criteria**

**6.1.1 Inclusion criteria**

- Preterm infants less than 31 weeks completed gestation at birth requiring mechanical ventilation and admitted to King’s NICU in the first 48 hours after birth
- Preterm infants less than 31 weeks completed gestation at birth requiring mechanical ventilation on day seven of life and beyond and who have not been eligible for recruitment to the study in the first 48 hours after birth

**6.1.2 Exclusion criteria**

- Preterm infants above 31 weeks completed gestation or term born infants
- Infants with major congenital abnormalities

**6.2 Sampling**

**6.2.1 Size of sample**

In a cohort of 368 preterm infants born between 24 to 30 weeks gestation, the standard deviation for the duration of mechanical ventilation was 3.83 days [11]. To detect a decrease in the duration of mechanical ventilation of three days with a power of 90% and a significance level of 5%, a sample size of 35 infants in each group would be required.

Historical data from our unit for the period 2015-2020 demonstrated that the median duration of mechanical ventilation for preterm infants born less than 31 weeks gestation was 12 days. Based on the unit’s clinical activity in the most recent years, more than 100 preterm infants less than 31 weeks completed gestation were admitted on average at King’s College Hospital over a twelve month period. An interim analysis will be carried out at half sample size to review if enough data have been gained at that point. The analysis will be performed by an independent researcher not involved in the project to avoid introducing bias to our data. The research team will be blinded to the results of the interim analysis unless there are any significant findings.

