# 4 STUDY DESIGN

This will be a randomised controlled trial. We aim to recruit a minimum of seventy premature ventilated infants born at less than 31 weeks gestation. Participants will be randomised to either closed-loop automated oxygen control or manually controlled oxygen from recruitment to successful extubation. We will also record basic epidemiologic parameters such as gestation at birth, birth weight, corrected gestational age, day of life and weight at study enrolment, use of antenatal steroids, mode of delivery, doses of surfactant administered, birth plurality and associated comorbidities that may impact on the duration of mechanical ventilation such as open ductus arteriosus and current evidence of infection.

Infants with known congenital anomalies will be excluded from the study.

Informed written consent will be requested from the parents or legal guardians of the infants and the attending Neonatal Consultant will be requested to assent to the study.

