Continuous data will be compared between infants in the intervention group (closed-loop automated oxygen control) and infants in the control group (manual oxygen control). Student's t test will be used for normally distributed data and Mann-Whitney U test for skewed data. Categorical data will be assessed using the Fisher two tailed exact test. P values less that 0.05 will be considered statistically significant. Statistical analyses will be performed using SPSS software (SPSS Inc, Chicago, Illinois, USA).

Notes will be stored in a locked filling cabinet. All identifiable information will be stored in password protected computers and on encrypted devices.

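### The half-sample interim analysis can release significant findings, yet the only significance level in the protocol is an unadjusted 0.05; if that level serves at both looks, the type I error is about 8.3%, not 5%

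*Protocol*

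**What the plan says.** Section 6.2.1 (Size of sample) plans one interim look: "An interim analysis will be carried out at half sample size to review if enough data have been gained at that point". An independent researcher outside the project performs it. The same section then adds: "The research team will be blinded to the results of the interim analysis unless there are any significant findings".

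The only significance level for the analyses is in the statistics paragraph of the Methodology: "P values less that 0.05 will be considered statistically significant". That sentence is general. It neither mentions the interim nor makes an exception for it.

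The sample size is set "with a power of 90% and a significance level of 5"%. It uses a difference of three days and a standard deviation of 3.83 days, and arrives at 35 infants per group. It makes no mention of a second look.

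The section on study management committees says that the study has none at present. The protocol therefore names no body that would decide what the interim result means.

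**The concern.** An analysis that asks whether the data in hand suffice, and that releases results when they are significant, looks like a test of efficacy that could end the trial or support a claim. If both that test and the final one use 0.05, there are two chances of a false positive and the 5% in the sample size calculation no longer describes the design.

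Two things would be at stake. The first is the error rate of the primary comparison, which could not be repaired convincingly once the interim result had been seen. The second is the size of the reported effect: with about 35 infants only a large observed difference reaches P<0.05, so a trial that stopped there would tend to overstate the benefit.

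**Working it through.** **Inputs.** From section 6.2.1: difference 3 days, SD 3.83 days, power 90%, significance level 5%, 35 per group, one interim at half the sample. From the Methodology: significance at P<0.05; Student's t test or Mann-Whitney U. Equal information per infant is assumed, so the interim is at information fraction 0.5.

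**1. The protocol's own sample size.** n per group = 2(1.960 + 1.282)² × 3.83² / 3² = 34.25, rounded up to 35. This matches the protocol. The one-sided version gives 28, so the stated 5% is two-sided. Power with 35 per group, by normal approximation: standard error = 3.83 × √(2/35) = 0.916; 3/0.916 = 3.277; power = Φ(3.277 − 1.960) = 90.6%. (The exact t test gives 89.8%.) The calculation is for one look, with nothing set aside for an interim.

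**2. Type I error with two looks at 0.05.** Under no effect, the interim and final statistics Z₁ and Z₂ are bivariate normal with correlation √0.5 = 0.707. The overall error is

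1 − P(|Z₁| < 1.96 and |Z₂| < 1.96) = 8.31%.

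Simulation of t tests with 17 or 18 per arm at the interim and 35 per arm at the end gives 8.3 to 8.4%. Simulation of Mann-Whitney tests on skewed (lognormal) data gives 7.9%.

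**3. Chance of P<0.05 at the interim if the planned effect is real.** With 17 and 18 infants, the standard error is 3.83 × √(1/17 + 1/18) = 1.295. The noncentrality is 3/1.295 = 2.316, on 33 degrees of freedom, with critical value 2.035. The noncentral t distribution gives 61%.

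**4. Average estimate among those results.** Simulating the same comparison and keeping only the trials with P<0.05 gives a mean difference of about 3.8 days, against a true 3.0.

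**5. Boundaries that keep the error at 5%.** These use the same bivariate normal calculation. For power, the means are 3.277 × √0.5 = 2.317 at the interim and 3.277 at the end.

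| Interim P / final P | Overall type I error | Power |
| --- | --- | --- |
| none / 0.05 (one look) | 5.00% | 90.6% |
| 0.05 / 0.05 | 8.31% | not a valid 5% design |
| 0.001 / 0.0495 | 4.97% | 90.5% |
| 0.0052 / 0.0480 (O'Brien-Fleming) | 5.00% | 90.4% |

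**6. Chance of crossing at the interim under those boundaries.** Repeating step 3 with critical value 3.611 (P<0.001) gives about 12%. With 2.993 (P<0.0052) it gives about 27%.

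**The case against.** The strongest reply is that 8.3% is conditional. No sentence says that the trial stops at the interim, that a positive claim may be made there, or which outcome is tested. The stated purpose could be a check of data sufficiency. Significant findings are tied only to lifting the team's blinding and might include safety. The 0.05 in the Methodology is not expressly applied to the interim. If the interim cannot lead to an efficacy claim or an early stop, the error stays at 5%. All of this stands, and it means that 8.3% cannot be presented as the trial's established error rate. But releasing results because they are significant implies a test, and the reader is given no other level to apply.

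A second reply is that boundaries are often set in a statistical analysis plan, which is not shown here. That is fair as far as missing detail goes. The point here is narrower: the protocol itself fixes an interim look that can release significant results, a single unadjusted level, and a single-look sample size. A boundary set elsewhere would have to be reconciled with that text.

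Third, an independent researcher does the analysis and the team is otherwise blinded to the results. This limits bias in conduct; it does not control the error rate.

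Two stronger readings are tempting, and the protocol does not support them:

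- From "We aim to recruit a minimum of seventy premature ventilated infants born at less than 31 weeks gestation" a reader might infer further looks beyond 70 and a still higher error rate. No such look is planned. The Study Summary gives 70 infants and section 6.2.1 gives 35 per group, so the phrase reads naturally as a recruitment floor, and replacing it is not needed to control the error.
- A reader might infer that silence after the interim tells the team which way the data point. With a two-sided test, silence shows only that the threshold was not crossed, as it would under any sequential rule.

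**Conclusion.** The concern holds in conditional form. The protocol plans a look at half the sample that can release significant findings, gives 0.05 as its only level, and sizes the trial for one look at 5%. If P<0.05 at either look can support a positive claim or an early stop, which the wording suggests but does not state, the overall two-sided type I error is about 8.3%, or about 8% with Mann-Whitney on skewed data.

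These figures are for the primary outcome alone, with looks at half and full information. The 61% chance of P<0.05 at the interim and the mean estimate of about 3.8 days rest on the protocol's own 3 days and SD of 3.83. The overestimate matters only if the trial stops on that result.

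The text should be settled before the interim takes place, because a rule chosen after the result is known would carry little weight.

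**What to change.** Amend section 6.2.1 in one of two ways.

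1. **Keep an efficacy look.** State the interim boundary and the matching final level: for example, two-sided P<0.001 at the interim with 0.0495 at the end, or O'Brien-Fleming 0.0052 and 0.0480. State that efficacy results go to the research team only if that boundary is crossed, and make the general 0.05 sentence in the Methodology refer to these levels for the primary outcome.
2. **Make no efficacy comparison at the interim.** State that it reviews only recruitment, data completeness and safety, and keep the final test at 0.05.

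Either takes one or two sentences and leaves the sample size unchanged. Under the first, power falls from 90.6% to 90.5% or 90.4%, about 0.1 to 0.2 points. The chance of crossing at the interim under the planned effect falls from about 61% to about 12% (P<0.001) or 27% (P<0.0052). Under the second, power is unaffected, but the trial cannot stop early for efficacy.

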**ROLES AND RESPONSIBILITIES OF STUDY MANAGEMENT COMMITEES/GROUPS & INDIVIDUALS**

There are no committees or steering groups involved in the management of this study at present.

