Closed loop automated oxygen control (CLAC) systems use SpO_2_ values monitored in real time, to calculate and make an adjustment to the (FiO_2_) without any human intervention. The resultant change in SpO_2_ is monitored and further alterations to the FiO_2_ made as needed. Closed loop automated oxygen control systems may, therefore, provide a solution for the low compliance to target oxygen levels, reduce the need for manual adjustments (and hence workload) and decrease complications. Indeed, in a randomised crossover study, we demonstrated that during the automated oxygen control period, there were fewer prolonged desaturations, infants spent a higher proportion of the time within their target SpO_2_ range during and fewer manual adjustments were made to the inspired oxygen concentration [6]. Our literature review identified 18 studies and highlighted that CLAC was associated with an increased percentage of time spent within the target oxygen saturation range, but there were no data to determine whether CLAC would reduce important clinical outcomes [7]. A previous review of 16 studies highlighted that the studies of CLAC were very heterogenous for design, population size and device used and also emphasised none had demonstrated whether the clinical outcome of preterm infants was improved. In our study, we demonstrated that the inspired oxygen concentration was reduced more rapidly than compared to manual control; the inspired oxygen concentration is a major determinant of when infants are considered to be ready for extubation [8]. We, therefore, now propose to undertake a randomised controlled trial to determine if the use of CLAC is associated with a reduction in the duration of mechanical ventilation. This is an important outcome as we have demonstrated that infants ventilated for more that seven days develop BPD [9].

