**3.1** **Objectives**

The primary objective of this study is to compare the duration of mechanical ventilation in preterm infants receiving closed-loop automated oxygen control with those receiving manually-adjusted oxygenation.

Secondary objectives are to evaluate any differences between the two groups in time spent in target oxygen saturation ranges, incidence of hypoxia or hyperoxia, manual adjustments required by clinical staff and adverse outcomes including BPD (at 36 weeks post menstrual age), overall duration of oxygen supplementation and length of stay.

- 1. **Outcome**
- Our primary outcome is the duration of mechanical ventilation
- Secondary outcomes are:

-percentage of time spent in target saturation range

-time spent in hypoxia and hyperoxia

-number of manual adjustments required

-number of days on oxygen

-diagnosis of BPD at 36 weeks post menstrual age

-length of ICU stay

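### The interim blind lifts on any significant finding, with no outcome, boundary or stopping decision attached and no body to hold the results

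*Protocol*

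**What the plan says.** Section 6.2.1 places one interim analysis at half the sample, to judge whether enough data have been gained. An independent researcher performs it so that bias is avoided. The next sentence sets the disclosure rule: "The research team will be blinded to the results of the interim analysis unless there are any significant findings". It does not say which outcomes are examined, what counts as significant at that point, or whether recruitment goes on after disclosure.

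The only definition of significance is at the end of the Methodology text in section 4: P below 0.05, for comparisons in general. On oversight, the roles and responsibilities page states: "There are no committees or steering groups involved in the management of this study at present".

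Section 3.1 lists one primary and six secondary outcomes. Three of the secondaries concern oxygen control: "percentage of time spent in target saturation range", time in hypoxia and hyperoxia, and the number of manual adjustments. No masking is described, and only the intervention arm is connected to the closed-loop software.

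**The concern.** The independent analyst is there to keep interim results away from those running the trial. The exception undoes this when there is a result to act on. As written, a P value below 0.05 on any examined outcome would release results to the research team, whether or not the trial stops.

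This matters more than usual here. The allocated arm is visible at the cotside, and the primary outcome ends at extubation. The trial runs in a single unit, where the investigators also seek consent. The research fellow who conducts the study also does most of the analysis. A team that knows the direction of effect could, without intending to, alter whom it recruits, how it presents the study to parents, how it assesses outcomes and possibly when infants are extubated. The second part of the trial might then not estimate the same effect as the first.

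The point concerns who sees interim results. The effect of two looks on the type I error is a separate matter.

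**Working it through.** **Inputs.** From section 6.2.1: "To detect a decrease in the duration of mechanical ventilation of three days"; "the standard deviation for the duration of mechanical ventilation was 3.83 days"; 90% power; 5% significance; "a sample size of 35 infants in each group would be required". The threshold P<0.05 is from section 4. Effect sizes for the secondary outcomes are not given, so a range is assumed.

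**1. The plan's own figure.** n per group = 2[σ(z₀.₉₇₅ + z₀.₉₀)/δ]² = 2[3.83 × (1.960 + 1.282)/3]² = 34.25, rounded up to 35. The figure reproduces with a two-sided test; a one-sided test would give 28.

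**2. Primary outcome at the interim.** Half of 70 is 35 infants, or 17.5 per arm. The standardised effect is 3/3.83 = 0.783. The expected test statistic is 0.783 × √(17.5/2) = 0.783 × 2.958 = 2.317. The chance of P<0.05 is about Φ(2.317 − 1.960) = Φ(0.357) = 64%. With 17 or 18 per arm it is 63% or 65% by the normal approximation, and 60% or 63% by the t test. The range is therefore 60–65%. With no true effect it is 5%.

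**3. Oxygen-control secondaries, if tested.** Each of the three outcomes is given the same assumed standardised effect d. For independent outcomes the chance that at least one is significant is 1 − (1 − p)³, where p = Φ(2.958d − 1.960) + Φ(−2.958d − 1.960). For d = 0.5, p = 0.316 and the result is 1 − 0.684³ = 68%. Correlation lowers this. Simulation with a common correlation from 0.7 down to 0 gives:

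| Assumed d | One outcome alone (t test) | At least one of three |
| --- | --- | --- |
| 0.3 | 14% | 26–37% |
| 0.5 | 29–31% | 49–68% |
| 0.8 | 62–65% | 83–96% |

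**4. No effect on any of the seven listed outcomes.** If independent, 1 − 0.95⁷ = 30%. With common correlation of 0.3, 0.5 or 0.7, simulation gives 27%, 23% or 18%.

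**5. Infants exposed.** At most 70 − 35 = 35 are enrolled after the interim point. The number falls if the analysis waits for outcomes. An infant born at 24 weeks reaches the 36-week BPD assessment 12 weeks later. With even enrolment over the planned two years, 70 × 12/104 ≈ 8 more infants would enter meanwhile, leaving about 27.

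**The case against.** The strongest reply is that the sentence is being read uncharitably. It stands in the sample-size section, where duration of ventilation is the only outcome named, and the stated purpose is to see whether there are enough data. On that reading a significant finding means a primary result good enough to stop on, and disclosure coincides with stopping. This is a reasonable guess at the intention, but the text does not say it. No stopping rule is attached, and on the primary-only reading the trigger is still met 60–65% of the time under the design effect. A statistical analysis plan may name the interim outcome and boundary. Their absence is not held against the protocol here; the disclosure rule that it does state is.

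A reader might infer that a significant secondary result at half sample is likely, because the Background reports that in the earlier crossover study "infants spent a higher proportion of the time within their target SpO_2_ range" and fewer manual adjustments were made. The documents do not support that. They give direction only, with no effect size or SD. The study compared infants with themselves, so its effect does not carry over directly to 17 or 18 infants per arm. At d = 0.3 disclosure by this route is less likely than not. Nor does the protocol say that secondaries are tested at the interim.

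Two further replies stand in part. A significant result on time in target or manual adjustments would mostly confirm what the team already believes, so the more serious harm comes from disclosure of the primary result. The routes to bias are also partly limited: the clinical team identifies infants, all eligible infants are to be approached, extubation follows the unit's protocol, and oxygen data are exported from the ventilator.

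**Conclusion.** The point holds as a defect in a stated rule. Followed literally, section 6.2.1 can pass interim results to the research team while the trial still recruits, and nothing in the protocol prevents it.

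The firmest figure is 60–65% for the primary outcome alone. It assumes that the 3-day difference and the SD of 3.83 are true, that P<0.05 is the trigger, and that normal theory is adequate. A larger SD would lower it. The figures for secondaries are conditional on their being tested and on assumed effect sizes, and should be quoted only as a range.

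The absence of masking is inferred from the design. Bias after disclosure is a risk and is not demonstrated, and the 35 of 70 infants is an upper bound. It would go too far to say that the team will probably see interim results, or that the two halves would certainly estimate different effects. The sentence should be changed, since the change is small and the safeguard otherwise fails when it is needed.

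**What to change.** Replace the disclosure sentence in section 6.2.1 with:

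> The interim analysis covers the primary outcome and safety only, against a pre-set boundary. The independent researcher reports to a named recipient outside the research and clinical teams, who tells the research team only whether the trial continues or stops. No interim estimate, P value or secondary result is released to the research or clinical team unless the trial is stopped.

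The recipient's independence should be made explicit. Section 8.6 has the sponsor monitoring the study jointly with the chief investigator, so naming the sponsor alone would not show it. A message to continue still tells the team that the boundary was not crossed; that is unavoidable and reveals far less than the results would.

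The cost is a short text change, the choice of a boundary and the naming of one recipient. The independent researcher is already planned. The small downside is that the team does not see interim results early.

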**6.2.2 Sampling technique**

All eligible patients will be approached and included in the study following parents/legal guardians’ consent and assent of the attending Neonatal Consultant.

Parents of eligible patients will be approached and consented within 24 hours of initiation of mechanical ventilation or as soon as an infant is screened as eligible for the study on day seven of life and beyond. If preterm delivery is anticipated, parents may be approached antenatally and consented once the infant is mechanically ventilated at birth.

**6.3 Recruitment**

**6.3.1 Sample identification**

The clinical team will identify potential participants and alert the research team. The latter will not access any patient identifiable information or medical notes until parents/ legal guardians have consented.

No payment will be made to participants or their families as the study will not require any additional visits/ inconvenience.

